#### 1182 ***Safety Endpoints:***

1183 All safety assessments performed including adverse events (and separately shunt-dependent  
1184 hydrocephalus, bacterial meningitis), vital signs (blood pressure, pulse rate, respiratory rate  
1185 and body temperature), ECG, haematology and biochemistry will be descriptively  
1186 summarised. No formal analysis is intended.

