### **Preclinical data**

The prevention of cerebral vasoconstriction in dogs with subarachnoid haemorrhage by nicardipine-releasing implants comparable to NicaPlant® has been demonstrated in different published investigations. In addition, under conditions of global cerebral ischaemia, nicardipine was shown to improve cerebral blood flow and to prevent ischaemic cerebral tissue damage and improve recovery from damage in dogs, rats and gerbils *in vivo*. Furthermore, the pharmacodynamic activity of nicardipine as vasodilating agent has been demonstrated in various animal models as general vasodilatation and as vasodilatation with increase of blood flow in the arterial beds of different organs in rats, dogs and monkeys.

Secondary pharmacodynamic effects of nicardipine were seen as anti-oxidant and anti-neuroinflammatory activities, activities which may contribute to the therapeutic effect.

Published investigations on safety pharmacology demonstrated, in accordance with the investigations on primary pharmacology, a general improvement of blood flow in the major organ systems such as heart, central nervous system, gastrointestinal tract and kidneys. Under conditions of experimental infarction in the heart or central nervous system, nicardipine reduced the infarct size and improved tissue recovery as well as revascularisation. Besides a reduction of renal blood flow in hypertensive rabbits, which was not seen in normotensive rabbits, no adverse effects of nicardipine were seen in safety pharmacology studies.

Most probably based on the improved blood flow in major organs, nicardipine may reduce the toxicity of other drugs.

NicaPlant® brain local tolerance has been assessed in mice using implant slices. No development of local reactions was observed by intravital microscopy and by immunohistochemistry, while occurred the expected vasodilation.

Full details of the preclinical data are described in the Investigator's Brochure.

108 **Risks / benefits**

109 The potential therapeutic benefits of NicaPlant® outweigh any potential risks for patients with  
110 aSAH. NPRI has already demonstrated good safety and tolerability profiles with no drug-  
111 related adverse events; in particular, there have been no observed significant differences in  
112 the incidence of central nervous system infection or hydrocephalus. Furthermore, all previous  

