113 NPRI studies demonstrated prevention of CV in vessels adjacent to the site(s) of implantation  
114 and decreased cerebral infarction and DIND.

115 NicaPlant® is a pharmaceutical equivalent of the NPRI. It has the same shape and size,  
116 meaning the implantation procedure remains unchanged in risk profile from previous studies.  
117 The API (nicardipine free base) load is unchanged with a similar excipient composition  
118 leading to a comparable *in vitro* release profile.

119 Overall NicaPlant® was safe and well tolerated in the Phase IIa study. The patient number  
120 per group was too small to perform differential statistics but regarding the current safety data  
121 available, the potential therapeutic benefit still outweighs the potential risks. The implants  
122 have proven to be easy to implant, as stated by investigators, and the DSMB assessed the  
123 benefits and risks at every meeting before allowing the progression to the next dosing level.  
124 In the DSMB's final meeting, after reviewing adverse events and pharmacokinetics, the board  
125 decided that there seems to be no additional benefit after the dose progression from 10 to 13  
126 implants.

127  
128 The proposed clinical study is a randomised, single-blind, parallel-group design comparing  
129 NicaPlant® implants versus standard of care in 40 patients who have had aSAH.

130 The two groups of patients will be subjected to the following treatments:

131 • Standard of care plus NicaPlant®.

132 • Standard of care.

133 Both groups of patients will receive the standard of care according to treatment guidelines [8]  
134 and all further medical care will not be different between the groups. Patients in the  
135 interventional group will only in addition receive NicaPlant® implants.

136 NicaPlant® will be administered by placement during microsurgical clipping of the ruptured  
137 aneurysm in proximity to all of the exposed cerebral blood vessels.

138 Patients will be assessed to determine the efficacy of NicaPlant® application to reduce the  
139 occurrence of cerebral vasospasm and to prevent early morbidity/mortality following aSAH.  
140 Cerebral vasospasm will be assessed by analysis of angiograms to determine narrowing of the  
141 proximal blood vessels. A cerebral vasospasm is defined as lumen reduction  $\geq 33\%$

142 Safety assessments will be made to confirm the safety and tolerability of the selected dose of  

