## **STUDY OBJECTIVES AND ENDPOINTS**

### **Primary objective**

- To assess the efficacy of local nicardipine application via controlled-release polymers (NicaPlant®) in preventing the occurrence of cerebral vasospasm following aneurysmal Subarachnoid Haemorrhage (aSAH), by evaluating the incidence of moderate to severe cerebral angiographic vasospasm assessed by digital subtraction angiography (DSA).
- To assess the safety and tolerability of the selected dose of NicaPlant® (10 implants).

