## 340 **STUDY DESIGN**

### 341 **Overall study design and plan description**

342 This study is a randomised, single-blind, parallel-group design comparing 10 NicaPlant®  
343 implants / patient versus standard of care in overall 40 patients who have had aSAH.

344 The two groups of patients will be subjected to the following treatments:

- 345 • Standard of care plus NicaPlant®.
- 346 • Standard of care.

347 Both groups of patients will receive the standard of care according to treatment guidelines [8]  
348 and all further medical care will not be different between the groups. Patients in the  
349 interventional group will only in addition receive NicaPlant® implants.

350 NicaPlant® will be administered as per the implantation protocol, (in brief: by placement  
351 during microsurgical clipping of the ruptured aneurysm in proximity to all of the exposed  
352 cerebral blood vessels).

353 Patients will be assessed to determine the efficacy of NicaPlant® application to reduce the  
354 occurrence of angiographic cerebral vasospasm and to prevent early morbidity/mortality  
355 following aSAH. Cerebral vasospasm will be assessed by analysis of angiograms to  
356 determine narrowing of the proximal blood vessels.

357 Clinical Outcomes will be recorded at 12 weeks and 1 year (52 weeks) after the aSAH. Safety  
358 assessments will be made to confirm the safety and tolerability of the selected dose of  
359 NicaPlant®.

360 A data safety monitoring board (DSMB) will be set-up to monitor safety throughout the trial  
361 period and provide recommendations for any necessary actions. A steering committee will  
362 receive and review the blinded reports from the DSMB and take action as appropriate.

363 The DSMB will convene after 20 patients have been recruited and monitored to discharge, or  
364 day 21, whichever occurs earlier.

365 The final analysis will be carried out when the last patient completes the week 12 assessment,  
366 the database has been locked at this time point and unblinding has occurred. Data collected  
367 for patients at Week 52 after aSAH will be analysed and included as an addendum to the final  
368 report.

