### 1115 ***Null Hypothesis:***

1116 As this is an evaluation of the superiority of NicaPlant® over Standard of care. The Null  
1117 hypothesis assumed throughout that there is no difference between the active and control  
1118 groups for any of the assessments performed. The Alternative hypothesis is that the two  
1119 groups do in fact differ.

1120 A series of hypothesis tests and, where appropriate, supporting statistical models will be used  
1121 to investigate these differences. Where possible, indicators of statistical significance (p  
1122 values) will be quantified with estimates of the magnitude of the treatment differences and  
1123 supporting the 95% confidence intervals.

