### 1124 ***Data Descriptions:***

1125 Data will be summarised according to patient population (FAS/PP/Safety), dose group (10  
1126 Implant/Control), assessment (Visit 1-6 / day where appropriate) and time (where  
1127 appropriate). Data collected on visit 7 will be reported and analysed in an addendum to the  
1128 study report.

1129 Categorical variables will be summarised as proportions (with 95% Clopper-Pearson  
1130 confidence intervals) and frequencies (if appropriate) and as odds ratios (with 95% Wald  
1131 confidence intervals), where logistic regression models are used. Continuous variables will be  
1132 summarised as Least square means and 95% confidence intervals, where analysis of variance

1133 (ANOVA) models are used and then also as supporting descriptive statistics (n, mean,  
1134 median, standard deviation, minimum, and maximum). Graphical displays appropriate to  
1135 these types of data will be used to present important findings.

1136 ***Treatment Group Comparability:***

1137 Surgical details (including Clip ligation & Implantation) and measures at baseline (including:  
1138 demographics, medical history, concomitant medication, physical examination, pregnancy  
1139 test) will be summarised descriptively by treatment group (10 Implant/Control) and overall.  
1140 No formal comparisons of the treatment groups at baseline will be made.

1141 ***Efficacy Endpoints:***

1142 The primary efficacy endpoint is the incidence of cerebral angiographic vasospasm (moderate  
1143 or severe) at Day 8±1. This is considered a binary outcome and the difference between the 10  
1144 Implant and Control groups will be investigated using Fishers Exact test. Proportions in the  
1145 two groups with 95% Clopper-Pearson confidence intervals will be used to quantify the  
1146 magnitude of the difference. In case cerebral vasospasm (moderate or severe) is occurring  
1147 before day 8, this measurement will replace the assessment at day 8±1.

1148 A supporting Ordinal logistic regression model (utilising all classified categories) will also be  
1149 used to provide odds ratio estimates (+/-95% confidence intervals) for the treatment effect  
1150 and associated significance levels (p-values).

1151 Secondary endpoints include the:

1152 -Incidence of new cerebral infarcts on CT scan at day 14±1, or before patient discharge,  
1153 (compared post-treatment CT scan).

1154 Exploratory endpoints include the:

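### Safety is a primary objective that the design text says will be confirmed, but descriptive, within-arm summaries in 20 v 20 patients can only estimate it

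*Protocol*

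**What the plan says.** Protocol section 2 (Primary objective) lists efficacy against vasospasm and, beside it, "To assess the safety and tolerability of the selected dose of" NicaPlant (10 implants). The primary outcome endpoints in the same section include adverse events and name shunt-dependent hydrocephalus and bacterial meningitis separately.

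The design narrative is stronger than the objective. The Risks / benefits text in section 1 states: "Safety assessments will be made to confirm the safety and tolerability of the selected dose of" the product. Section 3 (Overall study design and plan description) repeats the statement.

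Section 11 contains four relevant statements:
- Power & Sample size derives 40 patients (20 per group) for the primary efficacy endpoint. No safety quantity enters.
- Safety Endpoints provides for descriptive summaries of all safety data and closes with "No formal analysis is intended".
- Data Descriptions, which covers the Safety population too, states: "Categorical variables will be summarised as proportions (with 95% Clopper-Pearson" confidence intervals. These are intervals for one proportion at a time.
- Null Hypothesis assumes no difference between the "groups for any of the assessments performed. The Alternative hypothesis is that the two" groups differ. It adds that, where possible, p values will be accompanied by estimates of the treatment difference and 95% confidence intervals.

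**The concern.** Confirming safety against a randomised control group requires a statement about the excess risk over control: how large an excess the data can rule out. The protocol plans no such quantity for safety. Per-arm exact intervals do not supply it, because two separate intervals do not bound the difference between the arms.

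This is more than detail left to a later statistical analysis plan. The Safety Endpoints paragraph affirmatively excludes formal analysis, while the Null Hypothesis paragraph, read literally, covers the safety assessments and promises difference estimates. An analyst following one passage would depart from the other.

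At stake is what may be said on one of the two primary objectives. The protocol stresses that the implant cannot be withdrawn once placed. If a similar-looking table were reported under the word *confirm*, it would claim more than 40 patients can show, and later risk-benefit statements could build on it.

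**Working it through.** **Inputs from the protocol.** 20 patients per arm; two-sided 5% level; Fisher's exact test for the primary efficacy endpoint; 20% v 70%; stated power 84%. The protocol gives no control-arm rate for any safety event, so the rates in step 4 are assumptions, from 2% to 30%.

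**1. Reproducing the stated figure.** Power = sum over x and y of Bin(x; 20, p_A) × Bin(y; 20, p_C), over all tables with Fisher p ≤ 0.05. With p_A = 0.20 and p_C = 0.70 this gives 84.6%, which agrees with the stated 84%. The same enumeration is used in step 4.

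**2. What the planned within-arm interval shows.** With 0/20 events, the Clopper-Pearson upper limit is 1 − 0.025^(1/20) = 16.8%. With 4/20 it runs from 5.7% to 43.7% in each arm. Neither is a limit on the difference.

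**3. What the difference would show.** The Newcombe upper limit is d + √[(u_A − p_A)² + (p_C − l_C)²], where l and u are Wilson limits, z² = 3.8415 and n = 20.
- 0 v 0: u = 3.8415/23.8415 = 0.161 and l = 0, so the upper limit is **+16 points**.
- 1 v 1: Wilson limits 0.009 to 0.236; √(0.186² + 0.041²) = 0.191, so **+19 points**.
- 4 v 4: Wilson limits 0.081 to 0.416; √(0.216² + 0.119²) = 0.247, so **+25 points**.
- An unequal example, 4 v 1: +15 points (−7 to +37), Fisher p = 0.34.

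The protocol allows up to 10 replacements. If these fell five to each arm and everyone stayed in the Safety set (25 v 25), the 0 v 0 limit would still be 3.8415/28.8415 = 13 points.

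**4. How often a real rise would show.** Fisher power at 20 v 20. The protocol does not plan this test for safety; it serves only as a measure of what the data can distinguish.

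| Assumed control rate | ×2 | ×3 | ×4 | ×5 |
|---|---|---|---|---|
| 2% | 0.1% | 0.4% | 1.2% | 2.9% |
| 5% | 1.7% | 7.0% | 16.8% | 29.9% |
| 10% | 7.2% | 24.2% | 49.2% | 74.2% |
| 15% | 12.4% | 44.3% | 79.7% | 96.6% |
| 20% | 19.2% | 65.0% | 96.1% | n/a |
| 30% | 34.7% | 97.9% | n/a | n/a |

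A doubling is usually missed at every assumed rate (power at most 35%). A tripling is usually missed up to a control rate of about 15% (power at most 44%). Larger multiples of common events are usually detected.

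**The case against.** The strongest reply has four parts.

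*The objective says assess, not confirm.* This is correct: the stronger verb appears only in the design narrative, and no passage sets a criterion for declaring safety confirmed. A reader might infer that an absence of visible or significant difference will be taken as proof of safety. The document does not say so, and since no safety test is planned, non-significance is not a planned output. The sentence on earlier implant studies, that "there have been no observed significant differences in" infection or hydrocephalus rates, may seem to show such reasoning. It is background, the underlying studies are not visible here, and the reference list includes a randomised double-blind trial. It does not establish a decision rule for this trial, and no rewording of it is asked for.

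*Some comparison and precision already exist.* The DSMB reviews unblinded data and may recommend a hold or stop if adverse events on the implant outnumber those on standard of care. The arms also get exact intervals. Both points stand, but the DSMB acts on clinical judgement without a reported estimate, and the intervals are within-arm.

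*Descriptive safety reporting is usual at this size, and interval choice belongs in the statistical analysis plan.* The first half stands: description is not itself the defect. The separate plan was not available and may add difference intervals. The protocol would still contain the mismatch in wording and the conflict between its Null Hypothesis and Safety Endpoints paragraphs.

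*The power figures concern an unplanned test.* This is also fair. The Newcombe limits in step 3 carry the point; the power table only illustrates it.

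**Conclusion.** The point holds as a mismatch between claim and method. Safety is a primary objective, the narrative says it will be confirmed, and the stated analysis yields no bound on the excess over control. Even identical counts in the two arms would leave roughly 16 to 25 points of excess risk unexcluded for counts of 0 to 4 per arm, so the design supports estimation only. The Null Hypothesis and Safety Endpoints paragraphs also need reconciling, although the qualifier *where possible* softens that conflict.

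The limits assume 20 patients per arm in the Safety set. The power statements rest on assumed control rates. A reader might conclude that any several-fold rise in harm would usually be missed, but the figures do not support that: power is 65% for 20% v 60% and 98% for 30% v 90%. Nor does the protocol say how common meningitis or hydrocephalus is without the implant, so nothing here depends on it.

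This is a cheap improvement. It does not affect the design or the efficacy analysis.

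**What to change.** 1. In section 11, Safety Endpoints, add the risk difference (implant minus control) with a 95% Newcombe or exact unconditional interval for bacterial meningitis, shunt-dependent hydrocephalus, death, and patients with at least one serious adverse event. Base the safety statement on the upper limit, in the form: an excess above X points is excluded.
2. In the Risks / benefits text of section 1 and in section 3, replace *confirm* with *describe and estimate*.
3. Align the Null Hypothesis paragraph with Safety Endpoints: either limit the null and the tests to efficacy, or state that safety differences are estimated with intervals and not tested.

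The cost is a few lines of wording and one extra table from data already collected, with no added patients or procedures. The downside is a less favourable safety claim.

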#### 1187 ***Pharmacokinetic (PK) Endpoints:***

1188 Samples taken for drug concentration estimation in plasma and CSF are obtained post-  
1189 surgery. Single plasma samples are obtained on day 8, 14 and 21 and on additional days when  
1190 blood samples are taken for medical reasons but only once per day with single CSF samples  
1191 obtained when feasible in patient provided for medical reasons with external ventricular drain  
1192 at each occurrence when the CSF is removed for medical reasons and up to day of discharge  
1193 or day 21.

1194 Multiple plasma samples are obtained on Implantation day at 0, 6, 12 and 24h post implant  
1195 ( $\pm 20$  minutes each) for evaluation of day 1 kinetics.

1196 Plasma and CSF samples will be used to determine the total exposure to drug (AUC for  
1197 multiple plasma samples and average concentration (Cav) for single CSF samples if sufficient  
1198 CSF data is obtained).

#### 1199 ***a. Drug Profiles:***

1200 Plasma - Individual patient plasma drug concentration profiles over time for the active  
1201 treatment group (10 Implant) will be presented graphically and in summary tables. These will  
1202 identify the dose group (10 Implant) and assessment day (day 1, 8, 14, 21 and additional  
1203 samples where appropriate) and where applicable sampling time (day 1: 0, 6, 12 and 24  
1204 hours).

1205 Overall mean profile summaries for plasma will be produced according to dose group (10  
1206 Implant ) and assessment day and time (where appropriate) for the relevant analysis set using  
1207 descriptive statistics (n, arithmetic mean, SD, min, median, max, geometric mean, and  
1208 coefficient of variation (CV)) and these will also be presented graphically using geometric  
1209 means with linear and semi-logarithmic scales.

1210 CSF – Individual patient CSF values will be listed by day, date and time and plotted  
1211 individually over time as appropriate.

1212 However, these values will only be descriptively and graphically summarised according to  
1213 the active treatment group (10 Implant) by day/visit if, prior to database lock, there is  
1214 considered sufficient data to present them in the final statistical and clinical study reports.

1215 ***b. PK Parameters:***

1216 Plasma - The individual drug profiles will then be used to derive the respective PK curve  
1217 parameters for each patient. This will involve non-compartmental methods.

1218 The overall mean PK parameter summaries for plasma (defined in Section 2.4) and will then  
1219 also be produced according to dose group (10 Implant) for the relevant analysis set, using  
1220 descriptive statistics (n, arithmetic mean, SD, min, median, max, geometric mean and CV).  
1221 Plasma PK parameters will be presented for both Day 1 kinetics (0-24 hours) and Day 1 – 21  
1222 whenever sufficient data is available. The  $AUC_{0-\infty}$ ,  $AUC_{0-t}$  and  $C_{max}$  plus other parameters  
1223 defined in Section 2.4 for plasma will also be presented graphically.

1224 Individual patient plasma PK parameter values will also be presented with the summary  
1225 tables.

1226 CSF – The  $C_{av}$  (Day 1 – 21) for CSF will be similarly presented to the plasma PK parameters  
1227 if, prior to database lock, there is considered sufficient CSF data to present the  $C_{av}$  in the final  
1228 statistical and clinical study reports. Individual patient  $C_{av}$  parameter values will be presented  
1229 if sufficient data is available.

1230 ***Pharmacodynamics Endpoints:***

1231 All PD endpoints will be summarised according to treatment group (10 Implant ) and  
1232 assessment day using descriptive statistics. Derived PD parameters will be similarly  
1233 described.

1234 The relationship between drug exposure and pharmacodynamic effect will be explored on an  
1235 individual patient by patient basis, using the pharmacokinetic drug concentration over time  
1236 profiles as well as pharmacokinetic exposure parameters (Plasma  $AUC_{0-t}$ ,  $AUC_{0-\infty}$  / CSF Day  
1237 1-21:  $C_{av}$ ).

1238 In addition, the influence of exposure on safety (occurrence of specific adverse events) and  
1239 efficacy measures (vasospasm) may also be investigated.

1240

1241 **ETHICS COMMITTEE / IRB APPROVAL**

1242 The study proposal will be submitted to the Independent Ethics Committee (IEC) in  
1243 accordance with the national requirements.

1244 The IEC shall give its opinion in writing before the clinical trial commences. The investigator  
1245 should provide written reports to the IEC annually or more frequently if requested on any  
1246 changes significantly affecting the conduct of the trial and / or increasing risk to the subjects.

1247

